### 6.3 Statistical Methods

**Primary Analyses:** We will examine between-group differences in opioid and BZD exposure associated with an increased risk of falls in the intervention and control groups. Analyses will be performed using the following intention-to-treat principle, and index dates for the intervention group will correspond to the date on which they first received any intervention-related clinical activity. Index dates for otherwise eligible patients from the control group will be chosen at random from each patients' set of clinic visits corresponding to an eligible intervention visit during the study period. Our primary hypotheses are:

- Relative to individuals in both control groups, individuals in both intervention groups will experience a significant reduction in the milligram equivalent exposure to opioids and BZDs during the 1-year follow-up period.

- Relative to individuals in both control groups, individuals in both intervention groups will experience a significantly greater discontinuation rate of opioids and BZDs during the follow-up period 181 to 360 days after index.

There are two overlapping groups of patients aged 65+ that will be included in this study: opioid users and BZD users. For each hypothesis, there will be separate models comparing the impact of the program on opioid users and BZD users. Patients who use both will appear in both models. To examine any differential impact of the program among patients who use both classes of medications, a sensitivity analysis will be performed and will include an indicator variable for patients who use both classes.

Generalized estimating equations (GEE, PROC GENMOD) will be used to create longitudinal pre-post model for the milligram equivalent exposure models. An identity link with a normal distribution will be used for milligram equivalent exposure. The functional form of the model is as follows:

$$\text{Eq. 1: } Y = \beta_0 + \beta_1 X_{\text{exp}} + \beta_2 X_{\text{period}} + \beta_3 X_{\text{exp} \times \text{period}} + \beta_n X_n + \epsilon$$

Where  $X_{\text{exp}}$  is the exposure group indicator,  $X_{\text{period}}$  is the pre-post indicator, and  $X_{\text{exp} \times \text{period}}$  is the period-by-treatment interaction indicator and, correspondingly,  $\beta_3$  is the parameter of the difference in outcome by period for the intervention group compared to the control.  $X_n$  represents a vector of covariates.

**Secondary Analyses:** Our secondary hypothesis is:

- Relative to individuals in both control groups, individuals in both intervention groups will experience a reduction in the risk of experiencing a fall following the index date.

Risk is operationalized as the odds of experiencing a fall in the 12-month post-index compared to the 12 months pre-index. The models used for this analysis match those in Equation 1, with the exception that the models for fall risk will use a log link with a binomial distribution instead of an identity link with a normal distribution.

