## 1 BACKGROUND AND RATIONALE

### 1.1 Introduction

Falls among older adults in the US account for 2.8 million injuries, 800,000 hospitalizations, and 28,000 deaths per year. US medical costs associated with falls now total approximately \$50 billion. More than 150 randomized trials document successful falls interventions. Observational studies show consistent associations between falls and certain medications. Thus, it is widely accepted that fall-related morbidity and mortality could be reduced if systems were in place to identify and intervene in falls risk. Unfortunately, most physicians do not routinely screen older patients for falls and with the shortage of physicians going into primary care, it is unlikely that screening will improve.

The University of North Carolina at Chapel Hill (UNC) School of Pharmacy pioneered an approach using community-based pharmacists to screen and identify older adults at risk. In our study, pharmacists identified 186 patients who were on a high-risk medication. Pharmacists then conducted a medication review using a clinical algorithm to guide the decision-making process. Twenty-five percent of the pharmacists' recommended medication changes were accepted by physicians. In our current, follow-up, CDC-funded study, the UNC Schools of Pharmacy and Medicine are using an enhanced service network of 65 pharmacies to mitigate the barriers faced by community pharmacists conducting medication reviews. As of March 1, 2018, 70% of qualified patients were screened by pharmacists and 56% received a medication review with recommendations for lower risk drugs. Of these, 35% of have been accepted by prescribers. These studies show that other members of a healthcare team,

specifically, pharmacists, can accurately identify older adults at risk for falls and communicate recommendations for medication changes.

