### **4.2 Screening/Baseline Visit Procedures and Observation Procedures for the Cluster-Randomized Trial:**

- (1) Randomize intervention and control clinics:** A list of clinics that are interested in participating will be compiled by the primary investigators. A member of the study team, [name], PhD, will use the random number generator built into SAS to randomize 10 clinics into treatment and 10 clinics into control groups. If the number of potentially eligible clinics exceeds 20, 20 clinics will be chosen at random, and this list will subsequently be divided into 10 random treatment clinics and 10 random controls. Results of randomization will be provided to the study coordinators, who will inform clinics of their status.

Data for all patients who meet inclusion criteria will be included in this analysis. This educational

intervention is intended to better inform providers in intervention clinics as to the fall-related risks associated with opioids and BZDs as well as best practices in deprescribing opioids and BZDs. A toolkit to support screening and deprescribing will also be provided to providers at intervention clinics. It is expected that providers will use this information to attempt deprescribing for any patients for whom they feel the benefits of deprescribing outweigh the risks. The study team will collect data from the EHR on all potentially eligible patients, regardless of any attempted deprescribing. The same data will be collected for patients who received care from treatment and control clinics.

**(2) Screen for risk of falling:** Intervention group clinics will be expected to screen all patients who appear on the baseline report for falls risk, questions if the patient has not already been screened previously, by using the STEADI screening questions. Each clinic will be allowed to determine how they will integrate these questions into the patient care process. Although the processes used to integrate the screening questions into patient care will vary across clinics, all clinics will be required to enter patient responses to the questions into the EHR, as is standard practice in all UNC HealthCare clinics.

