### **5 SCREENING AND MONITORING EVALUATIONS AND MEASUREMENTS (how measurements will be made)**

In addition to the focus group instruments and web-based surveys, the development of which are detailed in Section 3, the following outcomes will be used for the cluster-randomized trial.

**The primary outcome for this study is opioid and BZD exposure, as measured by dose and discontinuation rate. A secondary outcome variable is the rate of falls.** We will also evaluate providers' satisfaction with the deprescribing toolkit. For clinicians providing services at an Intervention Group clinic, we will assess three outcome variables that reflect the process of service delivery: (1) whether or not their patients received education on opioids and BZD and their relationship to falls; (2) whether or not the deprescribing toolkit was utilized as part of the deprescribing process; and (3) whether or not HCPs referred to deprescribing toolkit recommendations concerning medication and non-medications to reduce the patient's risk of falls.

➤ **Opioid and BZD Exposure:** The primary outcome of this study will be exposure to opioid and/or BZD. This will be measured in two ways: (1) dose and (2) discontinuation. We will convert all opioid prescriptions to morphine milligram equivalents (MME), and all BZD prescriptions to diazepam milligram equivalents (DME). The method for calculating MME is well-established, and recommended by the CDC for evaluating opioid-related complications. Calculating DME is analogous, and has been used in previous work to evaluate exposure to BZD and has been used previously to evaluate success of discontinuation interventions. For each class of medications, we will calculate milligram equivalents for all observable prescriptions in the 12 months prior to the index and in the 12 months

post-index. To create a more conservative estimate of the impact of the intervention, we will assume that any authorized refills were filled. [DATA SOURCE: Epic EHR]

Discontinuation will be defined as a lack of opioid or BZD prescription from 181 to 360 days after the index. It is acknowledged that the intervention may not have an immediate impact on opioid and BZD discontinuation as prescribers taper patients' doses down, therefore a gap is given to allow for tapering in advance of discontinuation. [DATA SOURCE: Epic EHR]

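### Section 6.3 gives intervention-clinic patients an index date only if they receive an intervention activity, while controls get one without that condition; this contradicts the intention-to-treat statement and the stated analysis population.

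*Protocol*

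**What the plan says.** Protocol Section 6.3 (Primary Analyses) opens with "Analyses will be performed using the following intention-to-treat principle" and, in the same sentence, continues "index dates for the intervention group will correspond to the date on which they first received any intervention-related clinical activity". For the control arm it says that index dates "will be chosen at random from each patients' set of clinic visits corresponding to an eligible intervention visit during the study period".

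Every trial outcome hangs on that date:

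- **Dose** (Section 5): the plan is to "calculate milligram equivalents for all observable prescriptions in the 12 months prior to the index and in the 12 months" after it.
- **Discontinuation** (Section 5): "Discontinuation will be defined as a lack of opioid or BZD prescription from 181 to 360 days after the index".
- **Falls** (Section 6.3, Secondary Analyses): the 12 months after index against the 12 months before.

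On who is analysed, Section 4.2(1) states that all patients meeting the inclusion criteria enter the analysis, and adds: "The study team will collect data from the EHR on all potentially eligible patients, regardless of any attempted deprescribing". The analysis exclusions in Section 3.3 are cancer, cognitive impairment, hospice care, skilled nursing residence and not speaking English. Not having received the intervention is not among them.

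**The concern.** An index date defined by receipt makes receipt a condition for being measured, and only in one arm. What happens to a listed patient in an intervention clinic depends on staff decisions taken after randomisation:

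- Screening is expected only where it has not been done before (Section 4.2(2)).
- Education of listed patients is encouraged rather than required (4.2(3)).
- Fall-prevention materials go to those the clinic thinks will benefit (4.2(4)).
- Use of the toolkit is optional (4.2(5)).

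If the patients who are reached differ in prognosis from those who are not, the intervention arm becomes a selected group set against unselected controls. Randomisation of clinics then no longer protects either primary hypothesis or the falls analysis.

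**Working it through.** **1. The passages side by side.** Take an eligible patient in an intervention clinic who is never screened, educated or reviewed during the year.

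- Section 6.3: no activity, so no index date. No substitute date is given.
- Sections 5 and 6.3: no index date, so no pre-period, no post-period and no window from day 181 to day 360.
- Section 4.2(1): the patient meets the inclusion criteria and is to be analysed.
- Section 3.3: no exclusion applies.

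The same patient in a control clinic with a corresponding visit gets an index date and is analysed. The four statements cannot all be carried out together.

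**2. Missing-data handling does not rescue it.** Section 6.7 uses no imputation and expects randomisation to balance missingness. Here the missingness arises in one arm only. GEE can use a patient with one missing outcome, but this patient has neither a pre nor a post value.

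**3. Possible size, discontinuation, no true effect.** The plan states no figure for this, so there is none to reproduce. Let s be the share approached, p1 the discontinuation risk in patients who are (or would be) approached, and p0 the risk in the rest. The analysed intervention arm shows p1. The control arm shows pC = s·p1 + (1 − s)·p0. The spurious odds ratio is [p1/(1 − p1)] / [pC/(1 − pC)].

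For s, the only related figures in the protocol are from the team's pharmacy programme (Section 1.1): "70% of qualified patients were screened by pharmacists and 56% received a medication review with recommendations for lower risk drugs". Applying 70% and 56% to these clinics is an assumption, and so are the risks. Because any activity sets the index, the 70% screened is the closer analogue.

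| p1 v p0 | pC at 70% | OR at 70% | pC at 56% | OR at 56% |
|---|---|---|---|---|
| 8% v 2% | 6.20% | 1.32 | 5.36% | 1.54 |
| 7% v 3% | 5.80% | 1.22 | 5.24% | 1.36 |
| 6% v 4% | 5.40% | 1.12 | 5.12% | 1.18 |
| equal | p1 | 1.00 | p1 | 1.00 |

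Example at 70%: pC = 0.70 × 0.08 + 0.30 × 0.02 = 0.062; OR = (0.08/0.92)/(0.062/0.938) = 1.32.

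With 1,500 patients per arm (half of 3,000), non-receipt would remove 0.30 × 1,500 = 450 or 0.44 × 1,500 = 660 intervention patients.

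**4. A second illustration, inside the protocol's risk range.** The control risks above lie slightly over the 0.020–0.050 assumed in Section 6.4.2. So suppose instead that 30% of patients are suitable for tapering, with discontinuation of 10% against 2% in the others. Then pC = 0.3 × 0.10 + 0.7 × 0.02 = 4.4%. Let half be approached, suitable patients twice as often:

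- approach probability, others: 0.5/(0.3 × 2 + 0.7) = 0.385; suitable: 0.769
- share suitable among those approached: 0.3 × 0.769/0.5 = 0.462
- intervention risk: 0.462 × 0.10 + 0.538 × 0.02 = 5.69%
- OR = (0.0569/0.9431)/(0.044/0.956) = 1.31

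A pooled two-proportion z test (two-sided 0.05, 750 v 1,500, clustering ignored) then declares a benefit about 28% of the time instead of 2.5%. Varying the share approached from 30% to 90%, and the preference for suitable patients from 1.5 to 3 times (approach probability capped at 1), gives odds ratios of 1.06 to 1.51 and false-positive rates of about 5% to 57%. With no preference the odds ratio is 1.00 and the rate 2.5%.

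**5. Timing, a lesser asymmetry.** One arm uses a first activity, the other a random visit. If k visits were spread evenly over a year and activity began at the first, the mean gap would be (1/2 − 1/(k + 1)) × 365 days: about 61 days for k = 2 and 110 for k = 4. This ignores the requirement that control visits correspond to an eligible intervention visit, which should narrow the gap by an amount the protocol does not let one calculate.

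**The case against.** The strongest reply is that the protocol nowhere says unapproached patients are dropped. Section 4.2(1) intends the opposite, the qualifying activity is broad and undefined, and the control rule's reference to an eligible intervention visit hints at a visit-based rule. If any eligible visit in a trained clinic counted, the problem would shrink. That is fair, and it is why the point is a contradiction and not a declared exclusion. But the text does not say this, and it supplies no fallback.

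Four stronger readings may tempt a reader, and the documents do not support them:

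- *That the analysed patients are those willing to taper.* Section 4.2(5) places the assessment of willingness in the discussion of a dose change. Screening or education would normally have set the index by then.
- *That the data-collection sentence in 4.2(1) itself contradicts 6.3.* A patient who is screened with no deprescribing attempt still has an index date. The conflict is with the statement about who enters the analysis.
- *That control dates are simply any random visit, falling mid-year.* "Index dates for otherwise eligible patients from the control group will be chosen at random" is only the start of that sentence; the visits must also correspond to eligible intervention visits.
- *That the bias certainly favours the intervention.* Providers choosing patients they think suitable makes this likely. They might instead start with high-dose patients who are harder to taper, and counting time in a trained clinic as pre-period would tend to dilute an effect.

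It can also be said that the pre-post model removes baseline differences (Section 6.6). For dose it removes stable ones, but not a differing readiness to taper. For discontinuation there is little to difference, since patients qualify as current users and the outcome is defined only after index.

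**Conclusion.** The point holds as an inconsistency in the protocol's own rules, and it touches both primary hypotheses and the falls outcome. The loss of untouched intervention patients follows necessarily from the index rule as written, though no sentence announces it.

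The consequence for the estimate is conditional. Where approached patients are more likely to discontinue anyway, the illustrations give a spurious odds ratio of roughly 1.1 to 1.5 under no effect. The upper part of that range overlaps the 1.30 to 2.0 for which Section 6.4.2 reports power. Where approach is unrelated to prognosis there is no bias, only fewer patients. These figures rest on assumed risks, on approach rates borrowed from a pharmacy programme or chosen for illustration, and on independent patients. No size is offered for the dose outcome, because the documents give nothing from which to derive one. The timing difference is secondary.

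**What to change.** In Section 6.3, replace the two index rules with one that does not depend on care received. The cleanest anchor is the launch date, applied to the list that Section 4.2(3) already defines for intervention clinics (aged 65 or over, on an opioid and/or BZD for more than 6 weeks). Generate the same list from the EHR for control clinics on the same date. Analyse every listed patient who meets the Section 3.3 criteria in the clinic's randomised arm. Report receipt of screening, education or review only as a process measure.

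The first eligible visit on or after launch is second best. It treats the arms alike, but it still depends on attendance and prescribing after launch, which trained clinics may influence.

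The cost is wording and programming. Section 4.2(1) already provides for the same data in both arms. There are two statistical downsides. The effect is diluted by patients who were not approached, which intention-to-treat accepts. And with a launch anchor, patients first seen late in the year have less time before or within the window from day 181 to day 360, which dilutes discontinuation further. A first-visit index can be kept as a sensitivity analysis to show how much this matters.

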## 6 STATISTICAL CONSIDERATION

Statistical considerations are described below for the primary and secondary outcomes from the cluster-randomized trials. No statistical analysis will be conducted with focus groups, and the surveys will be analyzed using descriptive statistics and bivariate assessments for pre-post change in provider knowledge, skills, and attitudes in management of opioids and BZDs between intervention and control clinics.

All hypothesis tests that are observed and deemed to be not statistically significant will be reported as being inconclusive. All statistical estimates of population parameters will be tabulated along with corresponding confidence intervals (CIs) and/or standard errors (SE). All hypothesis tests and tests for power are two-sided with an overall alpha of 0.05, unless otherwise specified.

**6.1 Primary Outcomes: Opioid and BZD exposure,** as defined by changes in milligram equivalents over time across control and intervention groups as well as discontinuation of opioids or BZDs. Outcomes are described in more detail in Section 6.3.

**6.2 Secondary Outcomes: Risk of Falls,** as defined by differences in rate of falls over time across control and intervention groups and described in more detail in Section 6.3.

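### The dual-user sensitivity analysis is meant to show a differential programme effect, but the one device it names, an indicator variable, does not estimate one

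*Protocol*

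**What the plan says.** Section 6.3 (Primary Analyses) fits separate models for opioid users and for benzodiazepine users. The two populations overlap: "Patients who use both will appear in both models".

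It then gives the purpose of an extra analysis, "To examine any differential impact of the program among patients who use both classes of medications", and the tool for it: "a sensitivity analysis will be performed and will include an indicator variable for patients who use both classes".

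Eq. 1, the model for milligram-equivalent exposure, has a group term, a period term and one product term, group x period. The coefficient of that product, beta 3, is the programme effect. Everything else enters through X_n, which "represents a vector of covariates", and so enters additively. On the scale of the outcome, "An identity link with a normal distribution will be used for milligram equivalent exposure".

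The protocol names no product of dual use with group, period or group x period, and describes no separate analysis of dual users. Section 6.3 gives no model form for discontinuation, the other primary outcome, which section 5 defines from prescriptions 181 to 360 days after index.

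**The concern.** A differential impact means that beta 3 takes one value in dual users and another in single-class users. A covariate shifts the mean level of the outcome but does not let beta 3 vary. An analyst who follows the sentence literally would add one variable to X_n and obtain two numbers, neither of which is the quantity sought: a coefficient for dual use that mostly describes level, and a single common programme effect.

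Two misreadings could follow. A beta 3 that does not move when the indicator is added could be reported as showing no differential impact. A large dual-use coefficient, which may only mean that dual users have a different average dose, could be reported as a different response to the programme.

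**Working it through.** No figure in the protocol depends on this point, so there is nothing to reproduce. The check is algebra, illustrated by simulation.

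**Inputs from the protocol.** Eq. 1 with an identity link and normal distribution (6.3); 3,000 patients (3.2); 20 clinics, from the plan to "randomize 10 clinics into treatment and 10 clinics into control groups" (4.2); one pre and one post period (6.3).

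**Assumed inputs, not in the protocol.** Dual-user share p of 10%, 20% or 30%; dual users' level 0.50 higher at baseline; SD 1; within-patient correlation 0.5; a small time-constant clinic effect; the true effects in the table.

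**Step 1: beta 3 with and without the indicator.** Dual use does not change between a patient's two periods. When both periods are observed for everyone, it drops out of the pre-post change, so adding it leaves the estimated beta 3 unchanged. With the same share p in both arms,

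beta 3 = (1 - p) x effect in single-class users + p x effect in dual users.

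For p = 0.20 with effects 0 and -0.60: 0.80 x 0 + 0.20 x (-0.60) = -0.12. With effects -0.30 and 0: 0.80 x (-0.30) + 0.20 x 0 = -0.24.

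**Step 2: what the indicator estimates.** Let d be the effect in dual users minus the effect in single-class users. The dual-minus-single difference in means is the level difference L in three of the four group-by-period cells, and L + d in the post-period intervention cell. With equal cells the coefficient is their average, L + d/4. For L = 0.50 and d = -0.60 this is 0.50 - 0.15 = 0.35. Since L is unknown in practice, d cannot be recovered from it.

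**Step 3: simulation.** 200 runs per scenario, least-squares point estimates (equal to identity-link GEE with an independence working correlation). Means over runs:

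| p | Effect, single | Effect, dual | Weighted average | beta 3, Eq. 1 | beta 3, with indicator | Indicator coefficient | Three-way term (true d) |
|---|---|---|---|---|---|---|---|
| 20% | -0.30 | -0.30 | -0.30 | -0.298 | -0.298 | 0.494 | 0.006 (0) |
| 20% | -0.30 | 0 | -0.24 | -0.238 | -0.238 | 0.576 | 0.297 (0.30) |
| 20% | -0.30 | -0.60 | -0.36 | -0.359 | -0.359 | 0.428 | -0.299 (-0.30) |
| 20% | 0 | -0.60 | -0.12 | -0.121 | -0.121 | 0.351 | -0.605 (-0.60) |
| 10% | 0 | -0.60 | -0.06 | -0.058 | -0.058 | 0.354 | -0.595 (-0.60) |
| 30% | 0 | -0.60 | -0.18 | -0.180 | -0.180 | 0.345 | -0.601 (-0.60) |

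The largest difference between the two beta 3 estimates in any run was about 2.5e-14, which is rounding error. The model with dual use, its two-way interactions and the three-way term recovers d; the indicator model does not.

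**Step 4: precision of the right term.** With equal variances, SE(three-way) / SE(beta 3) = sqrt(1/p + 1/(1 - p)):

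- p = 10%: sqrt(10 + 1.111) = 3.33
- p = 20%: sqrt(5 + 1.25) = 2.50
- p = 30%: sqrt(3.333 + 1.429) = 2.18

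**The case against.** The strongest reply is that the sentence says what the analysis will include, not all that it will contain. An interaction model also contains the indicator. The sentence precedes Eq. 1 and does not place the indicator in X_n. The protocol also uses the word indicator for a product: the group-by-period variable "is the period-by-treatment interaction indicator and, correspondingly" carries beta 3. The exact terms of a sensitivity model are often left to the SAP, which is not at hand.

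Part of this stands. A reader might infer that the protocol rules out an interaction; it does not. The point survives because the protocol states both an aim and a tool. It writes out the group x period product for the main effect but nothing comparable here, and the named tool, used by itself, does not meet the aim. That is a fault in the wording, beyond detail deferred to the SAP.

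It is also fair that the simulation rests on invented shares, level differences and effects, and puts all 3,000 patients in one model although the opioid and benzodiazepine models each use a subset. It illustrates an algebraic result and does not measure harm in this trial. The right term will be imprecise, and section 6 already says that non-significant tests are reported as inconclusive.

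**Conclusion.** The point holds, with modest severity. As worded, the sensitivity analysis gives no estimate of differential impact. It returns a dual-use coefficient that is mainly a level difference and a beta 3 that is a share-weighted average. This holds for any dual-user share; only the illustrative sizes depend on the assumptions. The exact equality of beta 3 needs complete pre and post data and an identity link. With missing periods beta 3 may move slightly, but an additive indicator still estimates no effect modification.

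Three stronger readings are not supported:

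- **That the primary result is compromised.** This is a secondary look, and the primary beta 3 is essentially untouched.
- **That beta 3 is the same wherever the effect lies.** It matches only when the weighted averages match: at 20% dual users, 0 and -0.60 look like a uniform -0.12, not like a uniform -0.30.
- **That dual users are the patients for whom the question matters most.** The protocol does not say so; it gives them one sensitivity analysis.

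**What to change.** Amend the sentence in section 6.3:

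- **Milligram-equivalent models:** dual use enters Eq. 1 with its interactions with group and with period, and with the group x period x dual-use term.
- **Discontinuation:** as this is a post-index outcome, the matching term is group x dual use; a three-way term with period does not fit it.
- **Reporting:** give the programme effect with its confidence interval for single-class and for dual users, and the interaction with its confidence interval. Label the analysis an exploratory one of effect modification, since it is not a sensitivity analysis in the usual sense.

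The cost is a sentence or two of protocol text and one model statement per outcome. No new data are needed, because each patient's use of both classes is already established from the EHR. The drawback is imprecision: a standard error about 2.2 to 3.3 times that of beta 3 over the assumed range of 30% down to 10% dual users. A wide interval must not be read as evidence of equal effects.
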